### Analysis

Baseline data will be summarized as the number of observations, means, standard deviations, medians, minimums and maximums where the data are continuous and as number of observations and frequencies where the data are categorical. Analyses will follow an intention to treat approach. There are five primary outcomes in the study: minutes of moderate-to-vigorous intensity physical activity, minutes of sedentary behaviour, variation in time to sleep, variation in time to wake, and sleep efficiency. The primary analysis will test for between-group differences across the four study assessment points using separate linear mixed models for each outcome, with fixed effects for treatment group (device-entered vs. user-entered), time (assessment 1, 2, 3 and 4) and their interaction. Since the standard errors of the fixed effects depend on the variance-covariance structure that is used in the analysis, several possible structures including models with multiple random effects (e.g., intercept, time) as well as inclusion of autocorrelated error structures (e.g., AR1, Toeplitz) will be examined. Based on Akaike Information Criterion (AIC) the most reasonable fitting model will be selected. The interaction term will be tested at 1 % to allow for increased type 1 error rates associated with multiple primary outcomes. Secondary analyses will examine changes in composite measures of the primary outcome variables and selected secondary outcomes at the 0.05 level of significance.

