^a^The Geneactiv is provided to participants to begin wearing at visit 1, 3, 5, and 7 respectively

The research assistant performing height, weight, waist circumference and blood pressure measures received training to perform these measures and will be blinded to participant group allocation. Participants will also be provided with a gift voucher to the value of $10 at the completion of each of assessments in visits 2, 4, 6, and 8. Following completion of measurements during visit 2 participants will be randomised to one of the intervention groups and provided with access to the *“Balanced”* app; participants allocated to the Device-entered self-monitoring group will be provided with a Fitbit (Charge HR) activity tracker.

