### Power and sample size

A statistician independent of the research team performed the power and sample size calculations were based on detecting between group differences in changes in physical activity (30 min difference, standard deviation = 30), sedentary behaviour (90 min difference, standard deviation =110), variation in time to sleep (30 min difference, standard deviation = 40), variation in time to wake (30 min difference, standard deviation = 35), and sleep efficiency (5 % difference, standard deviation = 5) at the end of the intervention. Assuming a correlation of 0.6 between the repeated measurements, a total sample of 48 participants will give the study 80 % power to detect a group by time interaction for each of the five primary outcome variables, using an alpha level of 0.01. Hence a minimum of 64 participants (32 per treatment arm) will be recruited into the study to allow for 35 % attrition over the study period.

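### The primary mixed model leaves the pre-randomisation mean free in each arm; this is valid, but less precise than constraining or adjusting for baseline

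*Protocol article*

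**What the plan says.** The Analysis section of the protocol article fits a separate linear mixed model to each of the five primary outcomes, "with fixed effects for treatment group (device-entered vs. user-entered), time (assessment 1, 2, 3 and 4) and their interaction". The covariance structure is chosen by AIC. On the test it says: "The interaction term will be tested at 1 % to allow for increased type 1 error rates associated with multiple primary outcomes". It names no baseline covariate and no constraint on the baseline means.

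The Study procedure section places allocation after the baseline assessment: "Following completion of measurements during visit 2 participants will be randomised to one of the intervention groups". The Randomisation section describes blocks of 4 and 6 and mentions no stratification.

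The Power and sample size section is framed as differences in change at the end of the intervention. It gives a correlation ("Assuming a correlation of 0.6 between the repeated measurements") and claims that "a total sample of 48 participants will give the study 80 % power to detect a group by time interaction for each of the five primary" endpoints at an alpha of 0.01.

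**The concern.** Assessment 1 enters the model as an outcome, and the group main effect lets the arms differ there. The group-by-time terms are then differences in change from baseline. Any chance imbalance at baseline is subtracted in full, although a correlation of 0.6 justifies subtracting only part of it. Because allocation follows the baseline measurement, the true baseline means are equal by design, and estimating a difference between them adds noise without protecting against anything.

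What is at stake is precision. The trial is small (32 per arm), has five primary outcomes and tests at 1 %, and the baseline accelerometer data that would recover the loss are collected anyway. The article writes out the fixed effects of the primary model, so the point concerns a stated choice and not a detail left to an unseen analysis plan.

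**Working it through.** **Inputs (Power and sample size section).** Correlation r = 0.6; alpha 0.01, taken as two-sided because the article does not say; 48 participants, taken as 24 per arm. Variation in time to sleep has the smallest standardised effect: "variation in time to sleep (30 min difference, standard deviation = 40", so d = 30/40 = 0.75. For comparison, "sedentary behaviour (90 min difference, standard deviation =110" gives d = 0.82 and "physical activity (30 min difference, standard deviation = 30" gives d = 1.00. Assumptions: the stated SD is that of a single measurement, and all pairs of assessments have correlation 0.6 (compound symmetry).

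**Step 1: reproduce the stated 48.** The variance factor (in units of SD²) for change from baseline to the mean of three follow-ups is (1 + 2r)/3 + 1 − 2r = 0.733 + 1 − 1.2 = 0.533. For d = 0.75 the noncentral t gives power 0.803 at 24 per arm and 0.781 at 23 per arm, so N = 48. The stated figure is therefore recovered with a free-baseline, change-type analysis.

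**Step 2: single contrasts, free baseline against baseline-adjusted.**

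| Contrast | Free baseline | Adjusted | Ratio |
|---|---|---|---|
| Week 9 | 2(1 − r) = 0.80 | 1 − r² = 0.64 | 0.80 |
| Mean of three follow-ups | 0.533 | (1 + 2r)/3 − r² = 0.373 | 0.70 |

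The week-9 variance falls by 20 %; since √0.80 = 0.894, the standard error falls by about 11 %. Estimating the extra coefficient at 24 per arm moves the ratio to about 0.82. In general the week-9 ratio is (1 + r)/2, so the variance reduction is 30 % at r = 0.4, 25 % at 0.5, 15 % at 0.7 and 10 % at 0.8.

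**Step 3: the test the plan names.** With time at four levels, the interaction is naturally a joint test on 3 degrees of freedom. Let δ be the vector of standardised group differences at weeks 3, 6 and 9. The noncentrality is λ = (n/2) δ′V⁻¹δ, with n = 24 and

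- free baseline: V = (1 − r)(I + J), so V⁻¹ = 2.5 (I − J/4);
- adjusted: V = (1 − r)I + (r − r²)J = 0.4 I + 0.24 J, so V⁻¹ = 2.5 (I − 0.2143 J).

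Here J is the 3 × 3 matrix of ones. For d = 0.75, (n/2) × 2.5 × d² = 16.875. Hence λ = 16.875 × (S₂ − c S₁²), where S₁ and S₂ are the sum and sum of squares of δ/d, and c is 0.25 (free) or 0.2143 (adjusted). Power uses the noncentral F with 3 and 138 degrees of freedom at 1 %.

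| Trajectory (δ/d) | S₁, S₂ | λ free | λ adjusted | Loss | Power free → adjusted |
|---|---|---|---|---|---|
| Week 9 only (0, 0, 1) | 1, 1 | 12.66 | 13.26 | 4.5 % | 0.66 → 0.69 |
| Linear (1/3, 2/3, 1) | 2, 1.556 | 9.38 | 11.79 | 20.5 % | 0.48 → 0.62 |
| Constant (1, 1, 1) | 3, 3 | 12.66 | 18.08 | 30 % | 0.66 → 0.86 |

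The gain on the planned test runs from slight to large, and depends on a trajectory that the protocol does not state.

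**The case against.** A group-by-time mixed model that includes baseline is common, and in a randomised trial it is unbiased with correct type I error. The power section is itself framed on differences in change and a group-by-time interaction, so design and analysis agree. All of this stands: the point is one of efficiency, and nothing in the document is contradicted.

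Four stronger readings are tempting, and the document does not support them.

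- A reader might take 20 % as the loss for the primary test. It belongs to the week-9 contrast at r = 0.6 and is a loss of inverse variance. For the joint interaction test the range is about 5 % to 30 % under compound symmetry.
- A reader might infer that the trial is underpowered because of this model. At 48 participants, power for variation in time to sleep is 0.59 (0.71 adjusted) on a week-9 change contrast, but 0.80 (0.94 adjusted) on the mean of three follow-ups. Because the second reading reproduces the stated 48, the model choice does not make the sample size statement wrong.
- A reader might expect the constrained model to rescue incomplete records. The planned mixed model already keeps participants with only a baseline or only a follow-up value.
- A reader might treat the constrained model and the baseline-as-covariate model as interchangeable. They are close when data are complete, but can differ when values are missing.

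**Conclusion.** The point holds as an inexpensive gain in precision, not as an error of validity. The planned model estimates a baseline group difference that randomisation makes unnecessary. Adjustment would reduce the variance of the week-9 difference by 20 % at r = 0.6 (10 % to 30 % for r from 0.8 to 0.4) and that of the mean-of-follow-ups difference by 30 %.

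The sizes rest on one planning correlation applied to all outcomes, on compound symmetry, on a two-sided 1 % test and on 24 per arm with complete data. The covariance structure finally selected by AIC may differ, and would change the figures.

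**What to change.** Keep the linear mixed model and the AIC-based choice of covariance structure. Constrain the two arms to a common mean at assessment 1 by dropping the group main effect there, and keep group-by-time terms for assessments 2, 3 and 4. State that these three terms are tested jointly at 1 % in place of the current interaction test, and report the week-9 contrast with its confidence interval. The tested terms must be named, because the size of the gain depends on them.

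Alternatively, model assessments 2 to 4 as outcomes with the baseline value as a covariate interacting with time; with complete data the results are nearly identical.

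The cost is one line of model specification, fixed before the data are analysed. No extra visits or measurements are needed, and the sample size statement does not have to change on account of this point.

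### The fixed 1 % test on each of five primary outcomes is valid, but Holm's step-down keeps the same 5 % familywise ceiling and is never less powerful

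*Protocol article*

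**What the plan says.** The Analysis section sets the family: "There are five primary outcomes in the study: minutes of moderate-to-vigorous intensity physical activity, minutes of sedentary behaviour, variation in time to sleep", then variation in time to wake and sleep efficiency. Each outcome is analysed on its own, by "separate linear mixed models for each outcome, with fixed effects for treatment group (device-entered vs. user-entered), time (assessment 1, 2, 3 and 4") and the group-by-time interaction. The decision rule is explicit and so is its reason: "The interaction term will be tested at 1 % to allow for increased type 1 error rates associated with multiple primary outcomes".

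The Power and sample size section claims 80 % power "for each of the five primary outcome variables, using an alpha level of 0.01", with 48 participants before attrition. The Methods/Design part of the Abstract repeats the 0.01 level.

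The article names neither Bonferroni nor a 5 % familywise rate. It describes no ordering or reuse of alpha across the five tests, and it does not promise simultaneous confidence intervals. The Participant recruitment section says that recruitment began in July 2015.

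**The concern.** A fixed 1 % per outcome spends 0.05/5 on every test, however many of the other tests succeed. Holm's procedure compares the ordered p-values with 0.05/5, 0.05/4, 0.05/3, 0.05/2 and 0.05/1, and stops at the first failure. It holds the familywise error at 5 % or below whatever the dependence between outcomes. That matters here because all five outcomes come from the same accelerometer record.

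The first Holm threshold equals the planned 1 %, so Holm can only add rejections. The stake is efficiency: a trial of 64 people may declare fewer of its primary outcomes significant than the same data would support at the same error ceiling.

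**Working it through.** **Inputs** (Power and sample size section):

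- The limiting outcome: "variation in time to sleep (30 min difference, standard deviation = 40").
- The other four, as δ/SD: 30/30 for physical activity, 90/110 for sedentary behaviour, 30/35 for time-to-wake variation and 5/5 for sleep efficiency.
- A within-person correlation of 0.6, and N = 48, that is 24 per arm.

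**Assumptions, because the article does not state them:** two-sided tests; the SDs apply to a single assessment; compound symmetry; correlation between the five outcomes of 0 or 0.3.

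**1. The alpha split.** 5 × 0.01 = 0.05. Under a global null with independent outcomes, 1 − 0.99⁵ = 4.9 %.

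**2. The plan's own N.** Power comes from a noncentral t with 2n − 2 = 46 df, critical value 2.687 and noncentrality δ / (SD × f × √(2/n)). The factor f depends on the contrast:

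- Mean of the three post-baseline assessments minus baseline: f = √((1 + 2 × 0.6)/3 + 1 − 2 × 0.6) = 0.730. For variation in time to sleep, the limiting outcome, 30 / (40 × 0.730 × √(2/24)) = 3.56 and power is 80.3 %. This reproduces N = 48.
- Week-9 change from baseline: f = √(2 × (1 − 0.6)) = 0.894. The noncentrality is 2.90 and power is 58.9 %.

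The article speaks both of differences at the end of the intervention and of a group-by-time interaction, so both contrasts are carried forward.

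**3. Fixed 1 % against Holm, all five planned effects real.** Monte Carlo, 200,000 to 300,000 replicates; the Holm range covers outcome correlations of 0.3 and 0.

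| Outcome | Mean-post contrast: 1 % → Holm | Week-9 contrast: 1 % → Holm |
|---|---|---|
| Physical activity | 97.7 → 99.2–99.5 % | 87.6 → 93.0–94.5 % |
| Sedentary behaviour | 87.8 → 95.5–96.2 % | 68.4 → 81.8–83.0 % |
| Variation in time to sleep | 80.3 → 92.5–93.0 % | 58.9 → 75.7–76.6 % |
| Variation in time to wake | 91.0 → 96.9–97.3 % | 73.4 → 84.8–86.2 % |
| Sleep efficiency | 97.7 → 99.3–99.5 % | 87.6 → 93.0–94.4 % |

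**4. Fewer true effects.** Gain in power for variation in time to sleep, in percentage points. The range covers which other outcomes respond and the two correlations.

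| True effects | Mean-post contrast | Week-9 contrast |
|---|---|---|
| 1 | 0.1 | 0.1 |
| 2 | 2.0–2.4 | 2.2–3.0 |
| 3 | 4.4–5.1 | 5.2–6.7 |
| 4 | 7.7–8.4 | 9.7–11.3 |
| 5 | 12–13 | 17–18 |

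**5. At least one significant primary outcome.** Identical under both rules in every scenario, because the smallest p-value faces 0.01 either way.

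**6. Familywise error.** Under the global null the two rules are identical (4.9 % at correlation 0, 3.9 % at 0.6). With some true effects Holm uses more of the ceiling. With three true effects at 80 % power and correlation 0.3, for example, the rate is 4.0 % against 2.0 %. The highest rate seen for Holm with some true effects was 4.7 %.

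**The case against.** The strongest reply is that nothing here is wrong. The 1 % rule controls type I error, was fixed in advance, and is the same in the abstract, the sample size and the analysis. It also lets each behaviour be judged without reference to the other four p-values. This stands, and it makes the point an improvement rather than a correction.

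A reader might infer that several effects must coexist because the app targets all three behaviours. The article does not support that. The Trial design section gives both arms the same intervention and varies only the self-monitoring method. The Background says that devices may also reduce the cognitive processing that self-monitoring involves, and calls the net impact unknown. The five-effect case is the article's planning scenario, not a forecast. With two or three true effects the gain is modest.

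A reader might also infer that the weaker primary outcomes miss the stated 80 %. That depends on the contrast: the week-9 change gives 59–73 % for three of them, but the mean-post contrast gives at least 80 % for all five. Neither is exactly the planned test, which is a 3-df interaction if time is categorical. Holm's advantage does not rest on this choice, because it acts on the p-values whatever test produces them; only its size does.

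Finally, the change is not free of cost. Recruitment has begun, so relaxing a primary decision rule needs a documented amendment, and 99 % intervals will sometimes disagree with the Holm decision.

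**Conclusion.** This is a cheap and worthwhile improvement to a valid rule. Holm at familywise 0.05 keeps the same ceiling under any dependence and is never less powerful than 1 % per outcome.

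If all five planned differences are real, with 24 per arm, two-sided tests and outcome correlation of 0 to 0.3, the weakest outcome gains about 12–13 points (mean-post contrast) or 17–18 points (week-9 contrast). With fewer true effects the gain shrinks as tabulated, to almost nothing with one. The chance of any significant primary outcome stays the same.

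The documents do not support a claim that error control fails or that the sample-size alpha is wrong.

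**What to change.** By a dated amendment, justified and made before any unblinded outcome data are seen, replace the 1 % clause in the Analysis section with: *The five interaction p-values will be tested by the Holm step-down procedure at a familywise alpha of 0.05.* Align the alpha statement in the abstract. Keep 0.01 in the Power and sample size section as a conservative planning value, since power at 0.01 is a lower bound under Holm.

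The change needs no further participants, data or modelling. It has two costs to state openly: 99 % confidence intervals reported alongside will not always match the Holm decision, and Holm uses more of the 5 % ceiling when some effects are real.

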## Discussion

Large proportions of the population report insufficient physical activity, high volumes of sedentary behaviour and poor sleep [8–13]. Consequently, interventions targeting these behaviours must have large reach, an objective that can be achieved by delivering interventions using technology-based approaches [26, 37]. Technology-based approaches also allow participants to access intervention materials at times and places convenient to them and do not require face to face contact which is a limitation of traditional practitioner delivered treatments e.g., behavioural change counselling [26, 37]. This study demonstrates the efficacy of a novel app-based multi-behaviour intervention to improve physical activity, sedentary behaviour and sleep quality.

An important aspect of this study is examining the relative efficacy two different approaches to self-monitoring behaviour: device-entered and user-entered. These approaches have been used previously in interventions seeking to improve physical activity and sleep, although their relatively efficacy to improve these behaviours has not been directly compared [28, 31, 93]. Examining differences in the efficacy of these self-monitoring approaches is important to inform future behaviour change interventions. Automated approaches reduce bias and burden associated with manual recording, but require resources with financial implications. It is therefore important to understand the relative efficacy on behaviour change.

Strengths of the study include a multi-behaviour approach targeting physical activity, sedentariness and sleep: this approach can leverage the potential for reciprocal effects among the three behaviours and the occurrence of any co-action effects that may occur [17, 18, 22, 90]. A further strength of the study is the recruitment of a population-based non clinical sample. Few studies have been conducted in populations who report poor sleep yet do not have a diagnosed sleep condition [17, 37], although over 20 % of the population report inadequate sleep, only approximately half of this is due to sleep conditions [94]. In addition, interventions using app-based interventions and/or website-based interventions frequently observe non-usage attrition over the first 4 weeks of the intervention period, yet do not assess behaviour change until well after non-usage attrition has occurred (e.g. 12 weeks) [28, 36, 38, 39]. A strength of this study is the timing of assessments which are intended to capture changes in behaviour and platform usage over a time period which is infrequently examined.

In summary this study simultaneously targets improvements in physical activity, sedentariness and sleep quality, and will provide important information on the efficacy of different self-monitoring strategies. A multiple behaviour intervention that can improve these behaviours and which has large reach, as provided by app-based delivery methods, has considerable potential given the health risks associated with these behaviours and the proportions of the population that engage in these behaviours in ways that adversely impact health.
